**Figure 1 F1:**
[figure not shown]
Flowchart of specific steps in the methodology.

### Participants

We will identify eligible patients based on the diagnostic description and *China Classification and Code of Diseases National Clinical Edition 2.0* (CCCDNCE 2.0), which is based on the *International Classification of Diseases, Tenth Revision*, (ICD-10) and *International Classification of Diseases, Eleventh Revision*, (ICD-11). Diagnoses of ACS (23), including ST-segment elevation myocardial infarction (STEMI), non-ST-segment elevation myocardial infarction (NSTEMI) and unstable angina (UA), will be made by the attending physician at either admission to the hospital or during discharge. The inclusion criteria and exclusion criteria of the study are shown in Table 1.

**Table 1 T1:** Inclusion criteria and exclusion criteria of the study.

**Inclusion criteria**	
i	Age > 18 years
ii	Adults with a primary diagnosis of an ACS (23)
iii	Did not meet the diagnostic criteria for diabetes (24, 25) before the PCI surgery^*^, no history of taking hypoglycemic drugs or insulin
iv	Only have received the initial PCI
v	outpatient follow-up ≥12 months
vi	Volunteer to participate in the study

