## Introduction

Type 2 Diabetes mellitus (T2DM) is a major health concern worldwide, with a prevalence of about 463 million by 2019, and a 62% increase since 2009 (1). In Chinese adults, the estimated T2DM and pre-T2DM prevalence are 10.9% and 35.7% (2), respectively. It is a strong risk factor for cardiovascular artery disease (CAD) and major adverse cardiovascular events (MACE) (3–5). A pooled analysis involving more than 1 million participants in Asia found that patients with T2DM had a higher risk (hazard ratio, 1.89) of all-cause death than those without T2DM (6). People are conferred an eight fold increase in death risk by unrecognized myocardial infarction (MI) with diabetes (7). As patients with acute ST-segment elevation myocardial infarction (STEMI) significantly improved after percutaneous coronary intervention (PCI), the 10-year survival rate was nearly 76% (8). Prolonged life expectancy makes chronic care management after PCI a concern. Nearly half of the inpatients with MI complicated with T2DM (9, 10) and good blood glucose control is one of the keys. There have been multiple studies regarding clinical outcomes in patients after PCI with known T2DM (11, 12). Patients after PCI with chronic T2DM emerge with poor clinical outcomes and different treatment strategies (13, 14). Patients approximately 30% who underwent PCI suffer from diabetes (13). Considering the counter-balancing effects of hemorrhagic and ischemic complications, the recent ultra-short DAPT strategy may not be suitable for patients with T2DM (15). New-onset of diabetes after PCI (NODAP) has attracted much attention; a 5-year survival of patients after revascularization with diabetes were worse (16). Among 3,683 acute coronary syndrome (ACS) patients (without T2DM before PCI), 436 patients (11.8%) developed NODAP after a follow-up of 3.41 ± .9 years (10).

However, the risk factors and pathophysiological mechanisms for NODAP remain unknown. The risk factors for NODAP may be different from those for simple diabetes. Patients after PCI are generally elderly, and are associated with a variety of metabolic diseases (obesity, hyperlipidemia, etc.) and stress states related to surgery; all the above predict the risk of T2DM. Previous studies show that abnormal heart rate variability is a risk factor for diabetes (17), and heart rate variability (low SDNN) is common in patients undergoing PCI (18). High intensity statins (19, 20) also has adverse effects on diabetes.

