We propose leveraging advancements in machine learning by systematically comparing different modeling approaches (21), to develop a prognostic tool for NODAP. Therefore, we put forward the following hypothesis:

Refer to common risk factors such as obesity and smoking and explore the risk factors for NODAP; probing the risk of NODAP in different types of ACS patients (STEMI, NSTEMI, and UA) is equal or not.Systematically apply several machine learning algorithms to establish a predictive model of NODAP and verify its effectiveness.In this study, we sought to investigate the potential predictors of ACS patients with NODAP and comparatively evaluate performances of these predictive models with each other, to identify which is the most accurate.

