**Exclusion criteria**	
i	Have received coronary artery bypass grafting (CABG)
ii	Patients with severe hepatic and renal insufficiency, severe respiratory, hematonosis, tumor, autoimmune diseases, or multiple organ failure
iii	Patients with Alzheimer's disease, mental illness, or depression
iv	Being pregnant or lactating
v	Did not take secondary prevention^#^ for coronary heart disease after PCI (26)
vi	Participating in other clinical trials

* *Diagnostic criteria for diabetes: fasting blood glucose greater than 7.0 mmol/ L, HbA1c ≥6.5% (23)*.

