### Data

The data extracted from the hospital information system (HIS) will exclude the privacy of participants; detailed parameters will vary based on each institution, which may include outpatient and inpatient medical history and diagnostic imaging database. To ensure the unified management of mass data among multiple institutions, we have established a third-party data management platform (*http://121.30.232.162:10094/#/user/login?redirect=%2F*). Every participant will be assigned a systemic number separate from the medical record number. Based on the platform, the required information can be retrieved and excluded. After machine retrieval by a third-party platform, two researchers will review each participant for inclusion in the study.

Using data provided from decision support at four hospital sites, we expect at least eligible patients in the period 2010–2021, and data according to the fields included in the diagnosis (acute coronary syndrome, PCI, diabetes, etc.) and CCCDNCE 2.0 codes. A standardized case report form (CRF) that has been pilot tested and refined will be used for data extraction. Trained researchers will enter the identified data directly using the electronic CRF into the online platform managed in Beijing, China.

Data will be collected with traditional Chinese and western medicine characteristics that are important in the management of ACS patients with NODAP to confirm the baseline level and severity of blood stasis syndrome. Data will be included in two stages. First, ACS patients who were eligible for inclusion criteria were included. All these patients will be re-screened to ensure the duration of 12 months of follow-up and above. Structural data such as demographic information, diagnostic testing and medication situation can be directly collected in the database. Medical history and surgery records will be retained in the platform in unstructured text format. Researchers in charge of each institution will ensure consistency on extraction method and content, and train individuals for data identification and extraction, and entering DE identified data using the electronic CRF. Relevant medical history including history of ACS, history of T2DM, history of PCI surgery will be collected to confirm the diagnosis. New-onset diabetes was diagnosed by fasting blood glucose or HbA_1_c levels in the outpatient or inpatient biochemical test during follow-up.

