### Outcomes Measures

The outcome for each model will be the occurrence of NODAP. For reference, new-onset diabetes after organ transplantation mainly occurs 3–6 months after the operation, and the incidence drops to 4–6% 1 year after the operation (30). The onset of NODAP mainly occur within 1 year after the operation, thus the follow-up time of outpatient was determined to be no less than 12 months.

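### Criterion iii makes the PCI the cut between pre-existing and new-onset diabetes while the start of follow-up is undefined, so raised values first drawn after PCI in the index admission can enter as NODAP cases and can bias the ACS-type comparison

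*Protocol article*

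**What the plan says.** Inclusion criterion iii (Protocol article, Table 1) admits patients who "Did not meet the diagnostic criteria for diabetes (24, 25) before the PCI surgery". The footnote to Table 1 gives the limits: "Diagnostic criteria for diabetes: fasting blood glucose greater than 7.0 mmol/ L, HbA1c ≥6.5" per cent. The two limits are separated by a comma, with neither a joining word nor a repeat test.

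The Data section defines the outcome: "New-onset diabetes was diagnosed by fasting blood glucose or HbA_1_c levels in the outpatient or inpatient biochemical test during follow-up". Here the two tests are joined by a plain alternative, and inpatient tests are included.

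The only other timing statements concern duration. Criterion v requires "outpatient follow-up ≥12 months", and Outcomes Measures justifies this by saying that "The onset of NODAP mainly occur within 1 year after the operation". Neither says on which date follow-up begins.

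The first hypothesis in the Introduction includes "probing the risk of NODAP in different types of ACS patients (STEMI, NSTEMI, and UA) is equal or not". Table 2 lists fasting glucose and HbA1c among the predictors, without a sampling window.

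**The concern.** Every participant has an ACS and a PCI. The procedure is the only time anchor in the entry rule, and the outcome rule has none. The index admission is therefore split at the PCI, and the same fasting value can be handled in opposite ways on the two sides: drawn before, it can exclude; first drawn after, it leaves the patient eligible as non-diabetic and may lead to a case.

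Two results are at stake. First, cases that are really unrecognised diabetes, or a passing rise during acute illness, would enter the outcome used to train and validate every model. Second, the comparison of STEMI, NSTEMI and UA could show a difference produced by the order of blood draw and procedure and not by any difference in risk.

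The Introduction lists "stress states related to surgery" among features of patients after PCI, but as a predictor of diabetes. It does not discuss misclassification, and the Limitations section does not mention acute-phase hyperglycaemia.

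**Working it through.** **Inputs from the article.** PCIs: 10,000 to 15,000. NODAP: 6.1% to 11.6%, at least 610 patients (Sample Size). The stated minimum reproduces: 10,000 × 0.061 = 610. No sample-size figure is disputed here.

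**Inputs not in the article (assumed).**
- s: share of patients without diabetes who have a transient fasting glucose above 7.0 mmol/L in the index admission; 2% to 20%.
- q: share of these whose first fasting sample is drawn after PCI; 10% to 90%.

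**Model.** The true NODAP risk r is the same in two ACS types. The part s(1 − q) is drawn before PCI and excluded. The part s·q is drawn after PCI, stays in and is counted as a case.

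Observed risk = [(1 − s)r + s·q] / [(1 − s) + s·q]

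**Worked case, r = 6.1%, s = 5%.** (1 − s)r = 0.95 × 0.061 = 0.05795.
- q = 90%: (0.05795 + 0.045) / (0.95 + 0.045) = 0.10295 / 0.995 = 10.3%.
- q = 10%: (0.05795 + 0.005) / (0.95 + 0.005) = 0.06295 / 0.955 = 6.6%.
- When s and r are equal, the non-case terms cancel, so OR = 0.10295 / 0.06295 = 1.64.

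**Sensitivity to timing, s = 5%.**

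| q in the two types | r = 6.1% | r = 11.6% |
|---|---|---|
| 90% vs 10% | 10.3% vs 6.6%, OR 1.64 | 15.6% vs 12.1%, OR 1.35 |
| 70% vs 30% | 9.4% vs 7.6%, OR 1.27 | 14.7% vs 13.0%, OR 1.16 |
| 50% vs 50% | 8.5% vs 8.5%, OR 1.00 | 13.9% vs 13.9%, OR 1.00 |

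**Sensitivity to s, at 90% vs 10%.** For s from 2% to 20%, the OR runs from 1.26 to 3.33 at r = 6.1% and from 1.14 to 2.42 at r = 11.6%.

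**Equal timing, unequal frequency.** With q = 50% in both types but s = 10% vs 5%, the OR is 1.33 (r = 6.1%) or 1.21 (r = 11.6%).

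**No difference between types.** With equal s and equal q the comparison is unbiased, but incidence is still inflated: 6.1% becomes 8.5% at s = 5%, q = 50%.

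**Under symmetric handling.** If all index-admission values are baseline, the share s is removed whatever the draw order. Observed risk = (1 − s)r / (1 − s) = r, and the OR is 1.00.

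**If follow-up starts only after discharge.** Transient readings that have normalised drop out. The same formula then applies with s read as the share of patients with unrecognised, persisting hyperglycaemia who are detected at the first later test.

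**The case against.** The strongest reply is that follow-up elsewhere means outpatient follow-up (criterion v and Outcomes Measures), so it begins after the index stay, and the inpatient tests in the outcome definition are readmissions. Potential Risk Factors also separates initial information from outcome data, and Table 2 places fasting glucose and HbA1c with the former. On that reading a value drawn the morning after PCI is baseline and not an outcome.

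This is a fair reading and the text permits it. A reader might infer that the protocol makes such a patient a NODAP case on day 1; the documents allow that but do not state it. The reply does not remove the defect. Criterion iii still looks only at values before PCI. A patient whose first raised value comes after PCI still passes as non-diabetic and can become a case at the first outpatient test.

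A reader might also infer that the STEMI/NSTEMI/UA comparison is biased, in a known direction. The documents do not support this: they give no timing of PCI or blood draws by ACS type and no frequency of acute hyperglycaemia.

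The comma in the Table 1 footnote also matters. If both limits must be met at entry, a raised glucose alone would not bar entry even before PCI. The outcome needs only one of the two tests, so that glucose could later make a case; the asymmetry changes form but remains.

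Finally, Figure 1 is not shown, and a fuller protocol may define the window. That limits what can be said about missing detail. This point, however, concerns how the stated entry and outcome rules fit together.

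**Conclusion.** The concern holds in conditional form. As written, the entry and outcome rules do not treat index-admission values alike before and after PCI, so pre-existing or transient hyperglycaemia can be counted as NODAP and enter model training. This needs no difference between ACS types. Bias in the ACS-type comparison follows only if draw timing or the frequency of acute hyperglycaemia differs by type.

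The odds ratios are illustrations under assumed values, not estimates: at 5% transient readings and 6.1% true risk they run from 1.00 at equal timing to 1.64 at a 90% versus 10% split. They also assume that post-PCI index-admission values lead to cases, which the wording permits. The article describes its analyses as exploratory, but the ACS-type question is a stated hypothesis and the outcome definition feeds every model, so the rules should be corrected before extraction.

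**What to change.** In Table 1 (criterion iii) and the Data section:

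1. Treat every fasting glucose and HbA1c value from the index admission, before or after PCI, as baseline, in the same way for all ACS types.
2. Count NODAP only from tests after index discharge, with a pre-specified minimum interval chosen by the investigators.
3. State how baseline status is judged when fasting glucose and HbA1c disagree or HbA1c is missing. The second case matters because Limitations warns that the data are restricted to what the hospital systems hold. Say also whether the two limits in the Table 1 footnote are alternatives or are both required.
4. Add a sensitivity analysis that excludes patients classified only on an index-admission fasting glucose, and report the number reclassified by ACS type.

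The cost is revised wording and a date filter on data to be extracted anyway. The downside is somewhat fewer events: some early true cases will become baseline diabetes or be counted later, so the expected minimum of 610 should be rechecked once the rule is set.

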**Exclusion criteria**	
i	Have received coronary artery bypass grafting (CABG)
ii	Patients with severe hepatic and renal insufficiency, severe respiratory, hematonosis, tumor, autoimmune diseases, or multiple organ failure
iii	Patients with Alzheimer's disease, mental illness, or depression
iv	Being pregnant or lactating
v	Did not take secondary prevention^#^ for coronary heart disease after PCI (26)
vi	Participating in other clinical trials

* *Diagnostic criteria for diabetes: fasting blood glucose greater than 7.0 mmol/ L, HbA1c ≥6.5% (23)*.

# *Secondary prevention medications should include at least aspirin, P_2_Y_12_ receptor inhibitors, statins*.

### Patient and Public Involvement

The patients included in this study were not involved in the development of the informed consent and will not be involved in the conduct of the study. Given its retrospective nature, it does not involve collecting identifiable information such as name, medical record number, and genetic tests.

### Data

The data extracted from the hospital information system (HIS) will exclude the privacy of participants; detailed parameters will vary based on each institution, which may include outpatient and inpatient medical history and diagnostic imaging database. To ensure the unified management of mass data among multiple institutions, we have established a third-party data management platform (*http://121.30.232.162:10094/#/user/login?redirect=%2F*). Every participant will be assigned a systemic number separate from the medical record number. Based on the platform, the required information can be retrieved and excluded. After machine retrieval by a third-party platform, two researchers will review each participant for inclusion in the study.

Using data provided from decision support at four hospital sites, we expect at least eligible patients in the period 2010–2021, and data according to the fields included in the diagnosis (acute coronary syndrome, PCI, diabetes, etc.) and CCCDNCE 2.0 codes. A standardized case report form (CRF) that has been pilot tested and refined will be used for data extraction. Trained researchers will enter the identified data directly using the electronic CRF into the online platform managed in Beijing, China.

Data will be collected with traditional Chinese and western medicine characteristics that are important in the management of ACS patients with NODAP to confirm the baseline level and severity of blood stasis syndrome. Data will be included in two stages. First, ACS patients who were eligible for inclusion criteria were included. All these patients will be re-screened to ensure the duration of 12 months of follow-up and above. Structural data such as demographic information, diagnostic testing and medication situation can be directly collected in the database. Medical history and surgery records will be retained in the platform in unstructured text format. Researchers in charge of each institution will ensure consistency on extraction method and content, and train individuals for data identification and extraction, and entering DE identified data using the electronic CRF. Relevant medical history including history of ACS, history of T2DM, history of PCI surgery will be collected to confirm the diagnosis. New-onset diabetes was diagnosed by fasting blood glucose or HbA_1_c levels in the outpatient or inpatient biochemical test during follow-up.

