### Potential Risk Factors

As the study is primarily retrospective, multiple initial information data will be collected and outcome data will be divided into one dimension: new-onset diabetes. Initial information data for five broad categories include (I) demographic information; (ii) medical history; (iii) diagnostic testing; (iv) PCI surgery-related information; and (v) medication situation. Detailed information refer to previous studies on risk factors for diabetes (27, 28) (Table 2). Variables with missing data other than demographic information (age, sex, ethnicity, marital status) will be dealt with using multiple imputation (29).

**Table 2 T2:** Patient information to be extracted.

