### Sample Size

Based on prior studies and conditions of each hospital (31), the number of PCI surgical interventions is between 10,000 and 15,000 in the past 10 years and in which 6.1–11.6% patients (10, 32) may develop NODAP (at least 610 patients). For the exploratory analysis of multiple risk factors, ≥10 events per variable (EPV) are necessary to obtain sufficient degrees of freedom, with the assumption of at least 20 patients with the outcome (NODAP) per predictor variable (33). The ratio of the two groups is set to 5:5 (validation dataset: training dataset); the sample size could be calculated as 300 in both the training set and an internal validation set. The actual sample size may be larger than the calculated amount, thus it will be adjusted according to the situation.

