### Limitations

This study has some limitations. As the study is a non-randomized retrospective study, selection bias cannot be excluded. Based on diagnosis name or CCCDNCE 2.0 codes, eligible patients may miss some medical records that would have met eligibility criteria, including those that were given a broader diagnosis or incorrect ICD code. However, given a large number of sites and patients identified with decision support, we anticipated that only a small number of patients will be omitted. Given its retrospective design, included data will be limited by what is documented in the HIS, thus some of the data we are interested in cannot be obtained (e.g., waistline). Third, as an observational study, we were only able to address association rather than causation, if any predictors are identified with surgical outcome, education levels, or income levels. However, the analyses outlined are exploratory in nature. Fourth, given the 12-month follow-up period, it is not enough for all patients at risk to develop NODAP, which may act as unmeasured confounders.

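### No post-PCI glucose test is required and untested patients are left unclassified; if they count as non-cases, predictors linked to more testing can look like risk factors for NODAP

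*Protocol article*

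**What the plan says.** Four parts of the Protocol article bear on this.

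- **Entry.** Inclusion criterion v in Table 1 asks for "outpatient follow-up ≥12 months". The Outcomes Measures section gives the reason, the expected timing of onset, and concludes "thus the follow-up time of outpatient was determined to be no less than 12 months". Neither place mentions a glucose test.
- **Re-screen.** The Data section adds a second stage: "All these patients will be re-screened to ensure the duration of 12 months of follow-up and above". It checks duration only.
- **Ascertainment.** The Data section also states "New-onset diabetes was diagnosed by fasting blood glucose or HbA_1_c levels in the outpatient or inpatient biochemical test during follow-up". No schedule, window or minimum number of tests is given.
- **Outcome in the models.** Outcomes Measures says "The outcome for each model will be the occurrence of NODAP". Statistical Analysis models it by logistic regression, so each patient is either a case or a non-case.

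Two further sentences touch the matter without settling it. Under Potential Risk Factors: "Variables with missing data other than demographic information (age, sex, ethnicity, marital status) will be dealt with using multiple imputation". Under Limitations: "included data will be limited by what is documented in the HIS".

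**The concern.** Eligibility depends on attendance, while the outcome depends on testing. A patient seen for 12 months with no post-PCI fasting glucose or HbA1c on file meets the follow-up criterion, passes the re-screen and cannot be a case. The true status is unknown, yet the outcome has only two levels and no rule marks this patient as missing.

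Testing in routine care may well depend on the candidate predictors. Table 2 lists baseline glucose, BMI, family history of T2DM and statin intensity, all of which could plausibly prompt a test. The Data section also allows the available parameters to differ between institutions, while Table 2 lists neither site nor number of post-PCI tests.

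Three aims are exposed: identifying risk factors, comparing STEMI, NSTEMI and UA, and building a prediction model. The planned validation would not reveal the problem. Both halves of the 5:5 split, and every bootstrap sample, carry the same outcome error, so a model that partly predicts who is tested could still show a good ROC area.

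**Working it through.** **The plan's own figure.** Sample Size states that "the number of PCI surgical interventions is between 10,000 and 15,000 in the past 10 years" and takes a NODAP risk of 6.1% to 11.6%, with at least 610 patients affected. 10,000 × 0.061 = 610, and half of that is 305, close to the stated 300 per set if 300 is read as events. This point does not dispute those figures.

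**Inputs.** True risk r = 0.061 or 0.116 (Sample Size). The shares tested, t1 with a factor and t0 without it, are assumptions, because the article gives none. The factor has no effect (true odds ratio 1.00), and testing within each group is unrelated to true status.

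**Formula.** If untested patients are coded as non-cases, recorded risk = r × t, and the apparent odds ratio is [r·t1/(1 − r·t1)] ÷ [r·t0/(1 − r·t0)].

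Example with r = 0.061 and 90% versus 60% tested: recorded risks are 0.0549 and 0.0366; odds are 0.0549/0.9451 = 0.0581 and 0.0366/0.9634 = 0.0380; the ratio is 1.53.

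| Tested, with vs without factor | Recorded risks, r = 6.1% | OR | Recorded risks, r = 11.6% | OR |
|---|---|---|---|---|
| 95% vs 90% | 5.80%, 5.49% | 1.06 | 11.02%, 10.44% | 1.06 |
| 90% vs 80% | 5.49%, 4.88% | 1.13 | 10.44%, 9.28% | 1.14 |
| 80% vs 70% | 4.88%, 4.27% | 1.15 | 9.28%, 8.12% | 1.16 |
| 90% vs 70% | 5.49%, 4.27% | 1.30 | 10.44%, 8.12% | 1.32 |
| 90% vs 60% | 5.49%, 3.66% | 1.53 | 10.44%, 6.96% | 1.56 |

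**Would such a factor pass the plan's screens?** Take 10,000 patients, a training half of 5,000, and a factor that splits it into 2,500 and 2,500. This is before exclusions, so the chances below are upper limits for a 10,000-patient source. A two-proportion power calculation gives, across r = 6.1% to 11.6%:

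- 90% vs 80% tested: 16–28% chance of P < 0.05, and 5–12% of P < 0.01 (the univariate entry threshold).
- 90% vs 70%: 52–81% and 28–60%.
- 90% vs 60%: 87–99% and 70–96%.

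**Absolute risk.** With 30% untested overall and the same true risk in the untested, 0.061 × 0.70 = 0.0427, so 6.1% is recorded as about 4.3%. If 10% to 30% of cases go undetected, 610 expected events fall to 549 to 427.

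**Tested patients only.** Recorded cases r·t divided by patients tested t gives r in both groups, so the odds ratio returns to 1.00. This holds only if testing within each group is unrelated to true status.

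**The case against.** **The article does not say that untested patients are non-cases.** This is correct. A reader might infer that the plan counts them as free of NODAP, but no sentence does so. It is the likely default for a binary outcome read from laboratory records, not a stated rule, so the point is conditional.

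**An article may leave such coding to the full protocol, the CRF or the SAP.** The Data section describes a pilot-tested CRF and review of each participant by two researchers, and either could catch untested patients. Neither is said to. The entry, re-screen and ascertainment rules are all stated, and applying them as written leaves the gap. That makes it more than omitted detail.

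**Multiple imputation might cover the outcome.** The same paragraph mentions outcome data, and only demographics are carved out, so this reading is not excluded. But the sentence stands under Potential Risk Factors, and it could help only if untested patients were flagged as missing, which no rule does.

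**The distortion may be small.** A reader might also infer that heavily tested predictors will emerge as risk factors. That needs both the default coding and a material testing gap. Gaps of 5 to 10 points starting from 90–95% tested give odds ratios of only 1.06 to 1.14, usually not significant. Nothing in the article shows that gaps of 20 to 30 points exist.

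**If clinicians test those at higher risk, the untested hold fewer cases.** This stands too: the fall from 6.1% to 4.3% assumes equal risk in the untested and would then overstate the loss.

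**Limitations are disclosed.** The article concedes possible selection bias and dependence on what the hospital system records, and calls the analyses exploratory. It does not mention unequal glucose testing.

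**Conclusion.** The point holds in conditional form. The stated rules admit patients whose outcome was never measured, give them no classification, and make it impossible for them to be cases. If they end up among the non-cases, risk is understated, and a predictor with no effect can show an odds ratio of about 1.15 (80% vs 70% tested) to about 1.55 (90% vs 60%). These sizes rest on assumed testing rates and on testing unrelated to true status within groups. The article supports neither the statement that untested patients are counted as NODAP-free nor the statement that false risk factors will appear. It does support the statement that nothing in the plan prevents either. This should be corrected before outcome data are coded.

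**What to change.** In the Data section's re-screen, assign outcome status only to patients with at least one post-PCI fasting glucose or HbA1c in a follow-up window that is the same for cases and non-cases. Label the others outcome unknown, not non-case. Then:

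- extract the dates of post-PCI tests;
- report the share tested by site, ACS type and main predictors, and compare tested with untested patients at baseline;
- run sensitivity analyses that count the untested as non-cases, and that weight or impute their outcomes from baseline variables.

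The common window matters. Suppose cases qualified on a test at any time but non-cases needed one at or after month 12, with assumed shares of 70% ever tested and 50% tested at or after month 12. A true 6.1% would then become (0.061 × 0.70) ÷ (0.061 × 0.70 + 0.939 × 0.50) = 0.0427 ÷ 0.5122 = 8.3%, because retention would depend on the outcome.

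Do not adjust the main model for number of post-PCI tests. It arises after baseline, can be raised by the diagnosis itself and is unknown when predicting at PCI. Use it at most in a sensitivity analysis.

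The cost is a short addition to the outcome definition, one extra field from the laboratory records and a smaller analysed cohort. Some selection can remain if testing depends on true status beyond the measured predictors. One test also does not equalise the chance of detection between patients tested once and often, which is why the dates are needed.

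### The NODAP outcome counts laboratory values only, so a patient diagnosed and treated during follow-up can be coded as a non-case

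*Protocol article*

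**What the plan says.** **Outcome.** The Outcomes Measures section states: "The outcome for each model will be the occurrence of NODAP". It does not define the event further. The definition is in the Data section: "New-onset diabetes was diagnosed by fasting blood glucose" or HbA1c "levels in the outpatient or inpatient biochemical test during follow-up". This names two laboratory measures. It does not name a clinician's diagnosis, a diagnosis code or the start of a glucose-lowering drug.

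**Entry.** Table 1, inclusion criterion iii, has two parts. Before PCI the patient "Did not meet the diagnostic criteria for diabetes", and there must be "no history of taking hypoglycemic drugs or insulin".

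**Data extracted.** The medication row of Table 2 has statin intensity and traditional Chinese medicine (yes or no). Glucose-lowering drugs are not listed. The Data section does say that records are retrieved by diagnosis fields, diabetes among them, and by the national disease codes. It also says that history of T2DM is collected to confirm the diagnosis.

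**The concern.** Disease status is judged by one standard at entry and a narrower one at the end. Someone taking a glucose-lowering drug before PCI is excluded, because the drug history shows diabetes whatever the glucose value. Someone who starts such a drug after PCI is not recognised through that drug, only through a qualifying laboratory value in the study record. If the diagnosis was made without one, and treatment then keeps later values below threshold, the patient enters the analysis as a non-case.

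Every univariate test, odds ratio, ROC curve and model comparison in the plan uses this label. The random 5:5 split and the bootstrap cannot reveal the error, because the training and validation sets share the same outcome rule.

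**Working it through.** **1. The plan's own event count (Sample Size section).** The inputs are 10,000 to 15,000 PCI procedures and a NODAP rate of 6.1% to 11.6%.
- Minimum events: 10,000 × 0.061 = 610, which matches the plan.
- Half after the 5:5 split: 610 / 2 = 305, close to the stated 300.

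**2. Entry and outcome side by side.**

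| Evidence of diabetes | Used at entry (criterion iii) | Used for the outcome (Data) | Listed in Table 2 |
|---|---|---|---|
| Fasting glucose or HbA1c | yes | yes | yes |
| Glucose-lowering drug | yes | not named | no |
| Diagnosis field or code | used for retrieval | not named | not listed as a variable |

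**3. Missed cases.** Let m be the share of true cases that are first identified by diagnosis or treatment and never have a qualifying value on record. The documents give no figure, so m = 10% to 30% is assumed. Miscoded events = 610 × m.
- m = 10%: 61 events; observed rate 6.1% × 0.9 = 5.49%.
- m = 30%: 183 events; observed rate 6.1% × 0.7 = 4.27%.
- At a rate of 11.6% in 10,000 patients (1,160 events): 116 to 348 events.

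**4. Effect on an odds ratio (illustration).** Take two groups with true risks equal to the plan's two rates, 11.6% and 6.1%.
- True OR = (0.116/0.884) / (0.061/0.939) = 2.02.
- 30% missed in both groups: (0.0812/0.9188) / (0.0427/0.9573) = 1.98.
- 30% missed in the higher-risk group and 10% in the other: (0.0812/0.9188) / (0.0549/0.9451) = 1.52.
- The reverse: (0.1044/0.8956) / (0.0427/0.9573) = 2.61.

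Even under-detection lowers incidence but hardly moves the odds ratio. Under-detection that differs between groups moves it a good deal, in either direction.

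**5. Prevalent disease counted as new (secondary).** Criterion iii does not state that a measured baseline value must exist. Suppose a share q of included patients had undetected diabetes before PCI and all were later counted as new. Their share of counted cases = q / [q + (1 − q) × rate].
- Rate 6.1%: q = 1%, 2%, 5% gives 14%, 25%, 46%.
- Rate 11.6%: the same q gives 8%, 15%, 31%.

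These values of q are assumptions too.

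**The case against.** The strongest reply is that an article condenses its protocol and that a diagnosis route may already be present. Diabetes fields and codes drive the retrieval, and history of T2DM is collected to confirm the diagnosis. It is unclear whether that confirmation concerns entry or outcome. This softens the point but does not remove it: the article does state an outcome rule, that rule names laboratory values alone, and glucose-lowering drugs are absent from the extraction list.

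A second reply is that many treated patients will have a qualifying value recorded before treatment begins, and so will be counted. That is true, and it is why m is shown as a range. A third is that codes and prescriptions in four hospitals will not capture care given elsewhere. That also stands, and it limits the remedy.

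A reader might infer more than the text supports:
- *That one abnormal reading is stated to suffice.* The rule is silent on confirmation. It says fasting glucose, not any glucose, and it limits tests to follow-up.
- *That the protocol concedes false readings from acute stress.* The Introduction lists "stress states related to surgery" among predictors of T2DM risk, not as a source of spurious values.
- *That eligibility values are imputed.* The statement that missing data "will be dealt with using multiple imputation" stands under Potential Risk Factors and concerns variables in the model. Nothing applies it to entry.
- *That untested patients are admitted by rule.* Criterion iii does not demand a measured value, but it does not say that an absent result counts as negative, and two researchers review each inclusion.

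**Conclusion.** The point holds for the mismatch between entry and outcome. Followed as written, the rule codes as non-cases those patients whose diabetes shows only through a diagnosis or a treatment. On the plan's minimum of 610 events this is 61 to 183 miscoded events, if 10% to 30% of cases arise that way. The range is an assumption and takes the plan's event count at face value. The estimated incidence falls in proportion. The size and direction of bias in odds ratios and model performance depend on whether the missed cases are related to the predictors, which cannot be known from the documents.

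Proven misclassification in both directions is not supported. False positives from single or stress-related readings rest on what the rule leaves unsaid. Prevalent diabetes counted as new is a possibility that criterion iii leaves open; it merits a sensitivity analysis rather than a change to eligibility.

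**What to change.** 1. Define NODAP as the first of: a qualifying fasting glucose or HbA1c value after the index admission; a new diabetes diagnosis code; or a first recorded glucose-lowering prescription.
2. Add glucose-lowering drugs, with start dates, to Table 2 and the electronic CRF.
3. Keep the laboratory-only definition as a sensitivity analysis, so that the effect of the added routes is visible.
4. As further sensitivity analyses, restrict to patients with a measured (not imputed) pre-PCI fasting glucose or HbA1c and at least one follow-up test, and restrict laboratory cases to those confirmed by a second value.

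These changes fit the stated logistic regression. Diabetes fields and codes are already used for retrieval, so that route should cost little. The prescription route needs extra extraction, and its availability at each site must be checked. Diagnoses made outside the four hospitals may still be missed, which should be added to the Limitations. The restricted analyses will have fewer patients and events.
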